### Internal pilot

During the internal pilot, 40 children and families will be recruited in a sub-sample of CAMHS teams. During this phase any potential barriers to training, recruitment, intervention delivery or data collection will be identified. Towards the end of the delivery phase, a problem-solving workshop will be held in each site included in the pilot phase of the trial, attended by trial therapists, service managers and any other relevant CAMHS staff to gain feedback on training, recruitment, delivery of intervention, and supervision procedures. Any issues arising, as well as potential adaptations, will be discussed in meetings of the Trial Management Group and the TSC, both during and upon completion of the internal pilot. Any recommended changes will be implemented for the full trial. The MBT training team will also review levels of model fidelity during the pilot phase, including any items on the scale which had the lowest mean ratings, and any adaptations to training and/or supervision that should be made will be identified, to improve model fidelity in the main study.

The internal pilot will also be an opportunity to examine alternative approaches to the assessment of emotion regulation. Although multiple measures exist to assess ER in children, most clinical trials do not include the perspectives of both parents/carers and children. Moreover, recent research has highlighted the importance of assessing different components of ER if we are to understand how ER relates to psychopathology, and which aspects of ER need to be targeted in interventions. Due to the primarily deficit-focused approach in clinical psychology, the field has long neglected the role of adaptive ER, especially in youth populations. This is of particular importance, because recent evidence shows that the lack of adaptive–but not presence of maladaptive—ER was significantly associated with psychopathology for children with emotional disorders [58]. The pilot phase of this trial will therefore test the feasibility of evaluating different elements of ER, including self- and carer-reported assessment alongside task- and observation-based approaches. This will allow us to explore how different ER components relate to different symptom clusters and examine which aspects of ER change due to MBT treatment. If task- and observation-based approaches are shown to be feasible, and there is indication that they add an additional perspective to the assessment of ER, including co-regulation in the parent-child relationship, they will be included in the full trial.

Data collected in the internal pilot will be used in the analysis for the full RCT: participants recruited in the pilot will be included within the total number of participants for the full trial.

### Statistical plan and data analysis for main trial

#### Sample size and power calculation

The total sample size for the study will be 320. The power analysis was informed by an analysis of 71,763 UK CAMHS clinical records held by the Child Outcomes Research Consortium (CORC, https://www.corc.uk.net/), as well as by published psychotherapy trials in CAMHS settings. CORC data suggests that children meeting our inclusion criteria have a mean SDQ Total Difficulties score of 24.6 at presentation to CAMHS, with a standard deviation of 5.0. This score is our primary outcome. We assumed that the smallest clinically meaningful post-treatment difference on the SDQ is 1.5 points, which is equivalent to a standardised treatment effect difference of 0.3. The power analysis aimed to establish the number of children per therapist to give at least 80% power to detect this effect at the 5% significance level using a two-sided test. The statistical model will account for clustering of children within therapists, and of therapists within the CAMHS, via random intercepts. We will adjust for baseline SDQ scores.

We calculated the required sample size based on published formulae [59] and made the following assumptions: The within-patient correlation was assumed to be within-patient = 0.6, which is close to the median value of 0.59 estimated by a meta-analysis of within-patient correlations [60]. We estimated that 40 therapists will participate in the study and assumed a therapist effect of ICC therapist = 0.02. We think this ICC is conservative. There is little data on therapist ICCs in CAMHS settings specifically, but the recent Improving Mood with Psychoanalytic and Cognitive Therapies (IMPACT) trial, set in English CAMHS, reported ICC < 0.01 [61]. A smaller therapist ICC would increase power. The power analysis assumed that outcomes do not vary by CAMHS, which is also conservative. If there was intra-site correlation, power would increase, since each service would act as its own control. Given these assumptions, and allowing for 15% loss to follow-up, the total required sample size is *N* = 320 (160 children per treatment group, 8 children per therapist). The calculated power under this design is 80.8%.

### Statistical data analysis plan for the main trial

The primary analysis aims to establish the difference between the MBT and TAU groups in the SDQ Total Difficulties score at the end of treatment (16 weeks, Hypothesis 1). Children are clustered within therapists, who in turn are clustered within CAMH services. The primary analysis model is a linear mixed effects model, with random intercepts for therapists and services, controlling for SDQ and age group at baseline. The evidence for a difference in SDQ scores after treatment will be assessed via a two-sided t-test of the coefficient of the treatment indicator variable, using a parametric bootstrap to estimate standard errors. A 5% significance level will be used as a cut-off to support a finding of superiority of MBT over TAU.

Analogous models will be used to assess the evidence regarding a difference between the MBT and TAU groups with respect to secondary outcomes (Hypothesis 2).

To investigate potential mediation of the effect of MBT on child mental health via improvement in emotion regulation (Hypothesis 3), we will conduct a mediation analysis using treatment allocation as the exposure, the Emotion Awareness Questionnaire (EAQ) score as the mediator, and the SDQ Total Difficulties Score as the outcome. We will additionally adjust for both EAQ and SDQ scores at baseline. Summary scores from the validated scales will be used, rather than latent variable scores, in order to maintain consistency with the effect estimates of the primary analysis. We will conduct an analogous mediation analysis using parental emotion regulation, assessed by the Difficulties in Emotion Regulation Scale (DERS). More complex mediation models will be developed using exploratory analyses.

To examine whether the improvement in child SDQ Total Difficulties is clinically significant at the individual level, the reliable change index [62] will be calculated for each participant using the SDQ scores at baseline and post-intervention. Children will be classified as recovered, improved, unchanged, or deteriorated. We will compare the distribution of this classification in the MBT and TAU groups using an ordinal logistic regression model.

We will also estimate the difference in treatment effect between MBT and TAU on SDQ Total Difficulties and all secondary outcomes at 40-week follow-up, using statistical models analogous to those for the primary analysis.

All primary and secondary analyses will be carried out as intention-to-treat analyses. If some values at the primary endpoint are missing, the following strategy will be employed: 1) Evaluate likely processes of missingness and assess their potential for causing bias; 2) Conduct a complete cases analysis as the primary analysis; (3) Conduct information-anchored sensitivity analyses using controlled multiple imputation under MNAR assumptions to gauge the sensitivity of the trial results to potential violations in the MAR/MCAR assumptions [63, 64].

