### Outcome measures

Brief, well-validated tasks and questionnaires will be administered at four points: baseline, 8 weeks after start of treatment (mid-treatment), 16 weeks after start of treatment (end of treatment) and 40 weeks after start of treatment (follow-up). An overview of all assessment points and outcomes are detailed in the SPIRIT (Fig 1).

In order to maximize clinical validity, data will be gathered through multiple methods (including questionnaire, interview and observational assessments) and from multiple perspectives (including self- and carer-reports). A consensus-based standard set of international measures [41] has been used. All questionnaire measures selected have established reliability, validity, utility/practicability and acceptability for this age group; they have also been reviewed by our parent co-applicants to ensure that they are acceptable, relevant and culturally appropriate. The pilot phase of the study will be used to test the feasibility of online, task-based assessment of parent-child ER capacity and mentalizing.

Primary outcome measure: Parent-rated Strengths and Difficulties Questionnaire (SDQ) Total Difficulties Score [42]. The SDQ is one of the most widely used mental health measures for children in the UK, covering both emotional (anxiety and depression) and behavioural (ADHD and conduct) symptoms.

Secondary outcome measures will include a range of carer- and child-report assessments and tasks to assess:

Emotional and behavioural problems,
Me and My Feelings [43, 44], a brief 16-item self-report measure for children, including both emotional and behavioural sub-scales.Personalized treatment goals,
Goal Based Outcomes (parent/carer-defined) [45], a personalized goal-based measure completed by parent/carers.Parenting stress,
Parental Stress Index–Short Form [46, 47], a 36-item parent/carer-report measure of stress and the parent-child relationship.Parental mentalizing capacity,
Parental Reflective Functioning Questionnaire [48], an 18-item parent/carer-report measure of parental mentalizing.Service use and costs.

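### The primary 16-week analysis is fixed as complete-case and cannot use SDQ scores from other visits, so the planned 15% loss can bias the treatment effect if missingness works differently in the two arms

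*Protocol article*

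**What the plan says.** All references are to the protocol article.

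- **Statistical data analysis plan for the main trial, analysis principle:** "All primary and secondary analyses will be carried out as intention-to-treat analyses". ITT is not defined further.
- **Same section, missing 16-week values:** three steps are listed. The first is to evaluate how missingness arises and whether it could bias the result. The second is "Conduct a complete cases analysis as the primary analysis". The third is controlled multiple imputation under MNAR, as a sensitivity analysis. Nothing says that the first step can change the second.
- **Same section, primary model:** a linear mixed model for SDQ Total Difficulties at 16 weeks. It has random intercepts for therapist and service and adjusts for baseline SDQ and age group. There is no child-level term, and the 40-week SDQ is analysed separately with analogous models.
- **Outcome measures:** "Brief, well-validated tasks and questionnaires will be administered at four points", namely baseline and 8, 16 and 40 weeks. The SDQ is the primary outcome measure. Which instrument is given at which visit is in the SPIRIT figure, which is not reproduced in the text available.
- **Sample size and power calculation:** allows for 15% loss to follow-up.
- **Discontinuation and withdrawal:** families who stop treatment are invited to remain in the trial.
- **Blinding:** parents and children know their allocation. The primary outcome is parent-rated.

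**The concern.** A model for the 16-week score alone, fitted to complete cases, ignores everything observed after baseline in a child who lacks that score. The superiority claim rests on one 5% test in this model. If families who stop answering questionnaires are doing worse (or better) than those who continue, and this pattern is not the same in the two arms, the adjusted difference among completers is not the difference among all randomised children.

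Arm-specific patterns are credible here. The treatments differ, families know which one they have, and the person who decides whether to return the questionnaire is also the rater. The sample size covers the 15% loss as a loss of precision. It cannot cover it as a source of bias.

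The 40-week SDQ is certainly collected, and the 8-week SDQ apparently is. A MAR analysis could therefore use information that the stated rule discards.

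**Working it through.** **1. Inputs from the Sample size and power calculation.** Target difference: "the smallest clinically meaningful post-treatment difference on the SDQ is 1.5 points". Scores "with a standard deviation of 5.0". Within-patient correlation 0.6, described as "close to the median value of 0.59 estimated by a meta-analysis of within-patient correlations". Therapist ICC 0.02, 40 therapists, 8 children each, 160 per arm, 15% loss, test "at the 5% significance level using a two-sided test", and the aim "to give at least 80% power to detect this effect".

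**2. The plan's own figure.**
- Residual SD after baseline adjustment: 5 × √(1 − 0.6²) = 4.0.
- Children observed per arm: 160 × 0.85 = 136.
- Design effect: 1 + (8 − 1) × 0.02 = 1.14. With 6.8 observed children per therapist it is 1 + 5.8 × 0.02 = 1.116.
- Power with a t reference on 38 df (40 therapists − 2): 80.6% and 81.4% respectively. With a normal reference: 82.5% and 83.3%.

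The stated 80.8% is reproduced. It already assumes 136 observed children per arm, so the loss is paid for in power.

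**3. Children outside the primary estimate.** 0.15 × 320 = 48.

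**4. Bias of the complete-case estimate.** I simulated 1,000,000 children per scenario with baseline, 8-week and 16-week SDQ.
- *From the document:* SD 5, baseline to 16-week correlation 0.6, true 16-week effect −1.5, 15% overall loss.
- *Assumed, not in the document:* baseline to 8-week correlation 0.6; 8-week to 16-week correlation 0.6 or 0.75; 8-week effect half the 16-week effect; logistic dropout with slope 0.5 or 1.0 per SD of the driving score (odds ratio e^0.5 = 1.65 or e^1.0 = 2.72).

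The complete-case analysis regresses the 16-week score on arm and baseline. The comparator imputes missing 16-week scores within arm from baseline and the 8-week score (MAR). Clustering was left out, since it does not drive this bias.

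| Missingness | 8–16 week correlation | Complete-case estimate (truth −1.5) |
|---|---|---|
| Completely at random | 0.6 | −1.51 |
| Depends on baseline SDQ | 0.6 | −1.49 to −1.50 |
| Depends on 8-week SDQ, same slope and rate in both arms | 0.6 | −1.50 |
| Depends on 8-week SDQ in MBT only | 0.6 | −1.59 (slope 0.5), −1.67 (slope 1.0) |
| Opposite slopes in the two arms | 0.6 | −1.67 (slope 0.5), −1.81 (slope 1.0) |
| Same slope, loss 20% MBT / 10% TAU | 0.6 | −1.57 (slope 0.5), −1.60 (slope 1.0) |
| Same slope, loss 10% MBT / 20% TAU | 0.6 | −1.44 (slope 0.5), −1.41 (slope 1.0) |
| MBT only, slope 1.0 | 0.75 | −1.77 |
| Opposite slopes, slope 1.0 | 0.75 | −2.05 |

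The MAR analysis gave −1.49 to −1.52 throughout. With a true effect of zero and slope 1.0, complete case gave −0.15 (MBT only) and −0.31 (opposite slopes) at correlation 0.6, and −0.26 and −0.55 at 0.75.

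In the arm-specific rows the worse-scoring children are the ones lost from MBT, which flatters MBT. Reversing the pattern reverses the sign.

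**5. Effect on the test.** SE = 4.0 × √(2 × 1.116 / 136) = 0.512. For a bias b under no true effect, two-sided type I error = [1 − Φ(1.96 − b/0.512)] + Φ(−1.96 − b/0.512).
- b = 0.3: about 9%.
- b = 0.55: b/0.512 = 1.07, giving about 19%.
- If the bias instead shrinks a true 1.5 to 1.4, power falls from 83% to Φ(1.4/0.512 − 1.96) = 78%.

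**The case against.** The strongest defence is that the planned analysis is conventional and often unbiased. A baseline-adjusted single-visit model is valid under MAR given its covariates, it matches the power calculation, and MNAR sensitivity analyses are prespecified. The table supports this: bias is about zero in the first three rows. The larger figures rest on slopes, correlations and arm-specific patterns that the document does not supply, and the largest is an extreme case. All of this stands, and it limits the point to a conditional one. It does not remove it, because the sensitivity analyses do not replace the test on which superiority is declared.

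Four stronger readings are tempting and are not supported:

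- **The estimate is biased whenever dropout depends on the mid-treatment course.** Equal dependence and equal loss in both arms leave it essentially unbiased.
- **The ITT principle is breached.** The article does not define ITT as including every randomised child in the primary model. Nothing moves a child from the allocated arm, and follow-up continues after treatment stops. What is true is that the ITT label and the complete-case rule need reconciling.
- **The MNAR analyses have no MAR reference.** The article describes them as information-anchored and as testing departures from MAR/MCAR, so the primary model is the reference. The imputation model may be specified in an SAP that is not shown. The narrower fact is that no MAR analysis using other visits is named.
- **Children who never meet a therapist would fall out of the model.** The article does not say how they are handled, and this is ordinary SAP detail.

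Finally, an 8-week SDQ is inferred from the general schedule. The analyses that name the SDQ use baseline, 16 and 40 weeks. If the SDQ is not taken at 8 weeks, only the 40-week score remains as later information. The recovery shown for the MAR analysis would then not carry over in full; that case was not computed.

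**Conclusion.** The point holds in conditional form. The article itself fixes a complete-case primary analysis, and the stated model cannot draw on SDQ from other visits, so about 48 of 320 randomised children would be left out at the planned loss.

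Bias arises if dependence of missingness on post-baseline SDQ differs by arm, or if loss rates differ while such dependence is present. Under the assumed scenarios it is mostly about 0.1 to 0.3 points, or 7% to 20% of the 1.5-point target. It reaches about 0.55 points (37%) with opposite slopes of 1.0 per SD and a correlation of 0.75. It can run in either direction.

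The documents do not show that such missingness will occur, only that the design makes it plausible. This is a worthwhile and inexpensive improvement to the primary analysis rather than proof that the planned result would be wrong.

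**What to change.** Before any comparative outcome data are seen by those doing the analysis:

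1. **Primary estimate.** Use the 16-week MBT–TAU contrast from a linear mixed model on all collected post-baseline SDQ scores: 16 and 40 weeks, plus 8 weeks if the SPIRIT schedule confirms the SDQ is taken then. Include arm × time, baseline SDQ × time, age group, a within-child covariance across visits, and the planned therapist and service intercepts. An acceptable alternative is multiple imputation under MAR, done separately by arm, with the other visits' SDQ as auxiliary variables, followed by the planned 16-week model.
2. **Sensitivity analyses.** Keep the complete-case analysis as one of these, and define the MNAR imputations as departures from the MAR model.
3. **ITT wording.** State which randomised children enter the primary analysis and make the ITT label agree with it.
4. **Schedule.** State in the text which visits include the SDQ.

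The cost is revised protocol and SAP wording and a slightly larger model. No new data, visits or participants are needed.

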### Economic evaluation

The aim of the economic analysis will be to provide an assessment of the relative costs and benefits of MBT compared to TAU over the 40-week follow-up period. The study perspective will be that of the NHS and personal social services sectors, including those provided within the education sector. Health and social care service use will be collected using the CA-SUS questionnaire at baseline (covering the last 3 months) and at the 16- and 40-week follow-up points (covering the period since the last assessment). In addition, a Service Use Record will be completed by the CAMHS team at follow up to record the services offered and attended during the trial period. Collecting resource use at baseline will better characterise what ‘treatment as usual’ involves in terms of health care resources and allow for an adjustment for any potential baseline imbalances. Service use will be valued using PSSRU unit costs of health and social care [65] and national tariffs (NHS Reference Costs). MBT and TAU sessions will be costed using a bottom-up approach and using data on staff use (contacts). We will adopt a cost-consequences analysis (CCA) to report value for money of MBT versus TAU at 40 weeks. The CCA will report a disaggregated summary of all the costs and benefits of MBT versus TAU, without attempting to combine them into a single measure such as a cost-effectiveness or cost-utility ratio. This allows decision makers to decide which costs and benefits are most relevant to their decision context, and whether the relevant benefits are worth any additional costs that might be incurred. We will report mean costs and consequences, together with 95% confidence intervals, by treatment groups at baseline, 16 and 40 weeks. The consequences of interest for the CCA will be: SDQ and a range of carer and child-reported measures: The range of costs to be reported: intervention, medication, primary care, hospital care, social care, school-based service use. Costs and consequences will not be discounted given the short follow-up period.

#### Implementation and potential for scalability

A link to an online survey will be emailed to all stakeholders in the CAMHS taking part (practitioners, administrative staff, and managers) towards the end of the intervention phase to gain their views on the scalability of the MBT intervention at the end of the delivery phase of the full RCT. Once the online survey is completed, a single problem-solving workshop, including members of the research team, and selected practitioners, administrative staff, and managers, will be organised, in order to review the findings of the survey and discuss potential ways in which any identified barriers to post-trial implementation could be overcome, if the intervention is demonstrated to be effective.

### Trial oversight

A Trial Manager will oversee day-to-day management of the trial, with two research assistants. Trial staff will also include a statistician, a health economist, a clinical lead (with responsibility for training and ongoing supervision of CAMHS clinicians) and an expert by experience who will review all procedures and materials, Chair the Parent/Carer Advisory Group and help to problem solve operational issues. The principal and associated investigators will oversee all study operations. Clinical management will be provided by Leads in each CAMHS Trust. A Trial Management Committee will meet weekly to manage the day-to-day running of the trial (chief investigator, trial managers, research assistants, and site leads). A TSC will meet twice a year to provide oversight to ensure that the project is conducted according to the UK’s Research Governance Framework. A Data Monitoring and Ethics Committee (DMEC), comprised of experts who are independent of the sponsor (Anna Freud), will oversee progression of the data collection and undertake regular monitoring of the MBT intervention arm for signs of deterioration. This will be done by reviewing items on measures identified as markers of deterioration in the child. Unlike the TSC, the DMEC will have access to unblinded, comparative data. DMEC meetings will take place six-monthly, where required, once data collection has commenced, usually two weeks prior to TSC meetings in order for them to report to the TSC.

